## Abstract

**Background:**

Ethnic minorities with depression are more likely to seek mental health care through primary care providers (PCPs) than mental health specialists. However, both provider and patient-specific challenges exist. PCP-specific challenges include unfamiliarity with depressive symptom profiles in diverse patient populations, limited time to address mental health, and limited referral options for mental health care. Patient-specific challenges include stigma around mental health issues and reluctance to seek mental health treatment. To address these issues, we implemented a multi-component intervention for Asian American and Latino American primary care patients with depression at Massachusetts General Hospital (MGH).

**Methods/Design:**

We propose a randomized controlled trial to evaluate a culturally appropriate intervention to improve the diagnosis and treatment of depression in our target population. Our goals are to facilitate a) primary care providers' ability to provide appropriate, culturally informed care of depression, and b) patients' knowledge of and resources for receiving treatment for depression. Our two-year long intervention targets Asian American and Latino American adult (18 years of age or older) primary care patients at MGH screening positive for symptoms of depression. All eligible patients in the intervention arm of the study who screen positive will be offered a culturally focused psychiatric (CFP) consultation. Patients will meet with a study clinician and receive toolkits that include psychoeducational booklets, worksheets and community resources. Within two weeks of the initial consultation, patients will attend a follow-up visit with the CFP clinicians. Primary outcomes will determine the feasibility and cost associated with implementation of the service, and evaluate patient and provider satisfaction with the CFP service. Exploratory aims will describe the study population at screening, recruitment, and enrollment and identify which variables influenced patient participation in the program.

**Discussion:**

The study involves an innovative yet practical intervention that builds on existing resources and strives to improve quality of care for depression for minorities. Additionally, it complements the current movement in psychiatry to enhance the treatment of depression in primary care settings. If found beneficial, the intervention will serve as a model for care of Asian American and Latino American patients.

**Trial Registration:**

ClinicalTrials.gov: NCT01239407

## Background

The project proposes a randomized controlled trial to evaluate a culturally focused intervention to improve the recognition and treatment of depression in Asian American and Latino American primary care patients at Massachusetts General Hospital (MGH). The intervention entails using multi-lingual consultations and toolkits, for providers and patients, over the course of two visits. Goals of the project are to facilitate a) primary care providers' ability to provide appropriate, culturally informed care of depression in adult Asian American and Latino American patients, and b) patients' knowledge of and resources for receiving treatment for depression.

This intervention focuses on the primary care setting, as ethnic minorities with depression are much more likely to be cared for by primary care physicians (PCPs) than by specialists in mental health [1]. Targeting both the provider and patient in the intervention is important for a variety of reasons. Providers may face challenges in correctly diagnosing depression in patients whose ethnic background is different from their own, due to difficulties in correctly identifying depressive symptoms or using different cues or vocabulary to describe depression [2,3]. In addition, there may be some variation in symptom presentations. For example, Latino Americans may give greater emphasis to somatic complaints than non-Latino Caucasians [4], and as Asian Americans become more acculturated, they tend to report worsening levels of mood symptoms [5]. These varying symptom presentations can differ from what most clinicians are trained to expect, resulting in clinical misdiagnoses [6]. Patients themselves are reluctant to seek treatment; Asian Americans may experience higher levels of perceived stigma related to seeking mental health treatment, particularly from their families [7]. In addition, Latino Americans may have had fewer helpful mental health treatment experiences than non-Latino Caucasians, which may make them less willing to seek treatment in the future [8].

As one solution to bridge this gap between provider knowledge and patient needs, Kirmayer et al. developed the Cultural Consultation Service (CCS) model in 1999 [9,10]. The CCS responded to requests for assistance placed by primary care providers and mental health professionals facing difficulties with the assessment or treatment of ethnically diverse patients. In their evaluation of 100 cases referred to the CCS, Kirmayer's group found that cultural misunderstandings were associated with an increased risk for incomplete assessments, incorrect diagnoses, and inadequate or inappropriate treatment. By providing cultural consultations and formulations based on the DSM-IV cultural formulation model, the CCS effectively improved diagnostic assessment and treatment for their diverse population [9].

In a critical review of the literature, Van Voorhees et al evaluated interventions attempting to reduce disparities between non-Latino Caucasians and ethnic minorities and found that multi-component interventions were successful in improving depressive symptoms and functional status in nearly every study [11]. These interventions utilized a chronic disease management model, complete with case management, enhancement of access to care, and a variety of approaches tailored to the specific system, provider, and patient factors. One study, the "Improving Mood-Promoting Access to Collaborative Treatment" (IMPACT), not only improved all outcomes, but also eliminated ethnic disparities [12]. This trial randomized older adults with depression to usual care or to an intervention including case management, patient education, and either medication or problem-solving psychotherapy within a collaborative care model including available psychiatric consultation. The intervention demonstrated a reduction of depressed mood by at least 50 percent as compared to usual care; however, there was little cultural tailoring of the materials, i.e., the "matching of study intervention goals and materials to the needs and sensitivities of specific populations." In fact, Van Voorhees et al concluded that none of the studies in their review compared culturally tailored interventions with standard interventions in a randomized control trial. They also wondered if "structural changes in the pattern of delivery of mental health services" and "culturally tailored mental health service programs" may prove to be particularly effective to minorities impacted by mental health issues [11]. The proposed intervention seeks to provide such a model to Asian American and Latino American primary care patients - understudied populations in health care disparities intervention research [13,14].

### Preliminary Studies

The first part of the proposed intervention, conducting clinic-wide screening for depression, builds on the work by [name]. In one project using widespread depression screening in an Asian American population in primary care in 2004-2005, Yeung and colleagues [15] used a Chinese bilingual version of the Patient Health Questionnaire (CB-PHQ-9) to screen and identify patients with possible depression. Patients who screened positive were interviewed to establish psychiatric diagnosis and to engage them in treatment. Their work demonstrated that depression could be identified in this sample of primary care patients, using a translated screening questionnaire and a culturally sensitive clinical evaluation to engage patients in mental health treatment. In addition, 44% of those who screened positive agreed to come in to be assessed by a psychiatrist; among those who were then diagnosed with MDD, 93% were willing to accept treatment. These findings demonstrate that screening minority patients in primary care settings can be both a feasible and effective tool to identify patients likely to have clinical depression.

Mischoulon et al. reported that screening in primary care settings may not be enough; independent screening by psychiatrists in primary care settings may not be adequate to ensure appropriate management of depression by PCPs [16]. In this study, patients were screened for MDD in a community-based primary care health center. For those who met criteria for MDD, a letter was mailed to their PCP informing them of their patient's diagnosis of MDD. Forty outpatients, of whom 29 (72 percent) were Latino American, were found to meet criteria for MDD. Medical record charts were reviewed 3 months later to determine the PCPs' management following the diagnosis. Of the 38 patients who remained in the study at 3 months, 20 (53 percent) received no intervention for depression from the PCP, and of these, 14 (70 percent) were Latino American. Only five (13 percent) were prescribed an antidepressant by their PCP, nine (24 percent) were referred to mental health services for medication, psychotherapy or combination treatment, and four (11 percent) were prescribed an antidepressant and then referred to mental health services. Mischoulon and colleagues concluded that possible explanations for this lack of treatment of depression may include time constraints during primary care visits, patient and/or physician reticence, and insufficient education of PCPs about clinical depression. These findings suggest that screening and notification must be supplemented by additional interventions if they are to have an impact on the care of depression.

The second part of this proposed intervention derives from a pilot project from our group that applied a culturally focused psychiatric consultation service for a group of high service-utilization patients. In the initial pilot, the service was based on the Cultural Consultation Service (CCS) model developed by Kirmayer et al [9,10]. As part of the consultation service, members of the project team met monthly with case managers who were following a group of chronically, medically ill patients. Cases with difficult psychiatric issues were discussed, and formal consults could be requested for patients whose presentation and treatment was complicated by cultural issues. Members of the consultation service also met regularly to discuss cases. Results of the initial needs assessment indicated that case managers perceived a strong need for such a culturally focused psychiatric consultation service, but tended to refer patients for psychosocial issues rather than for psychiatric diagnostic assessment. Similarly, in a six-month follow-up to the culturally focused psychiatric clinical intervention, case managers were asked about their overall perception of the utility of the service and obstacles to its use. Based on their responses, case managers perceived a significant value, but tended to underutilize the service. This experience suggested four hypotheses. The consultation service would benefit from: a) focusing on a specific psychiatric diagnosis; b) targeting patients at their primary care providers' offices directly, providing a greater ability to connect with minority patients than an intervention that serves as a liaison to staff; c) making the consultation service more user-friendly; and d) enriching the intervention with patient-focused materials, in order to maximize patient knowledge and skills. These findings further supported the recruitment of patients through screening for those who meet criteria for likely depression, rather than relying solely on referrals by PCPs.

A final component of the CFP intervention was based on the team's experience with adapting cognitive behavioral interventions for the treatment of depressive disorders in chronically ill Latino Americans [17,18]. For example, in a sample of HIV-positive foreign-born Latino Americans, a cognitive behavioral intervention was linguistically/culturally adapted and administered by bilingual/bicultural staff. Participants received either a 10-week cognitive behavioral stress management (CBSM) intervention or a one-day seminar. Results indicated that, compared to those who only received the seminar, participants who received the CBSM intervention reported significantly less anger, maladaptive coping, and HIV-related symptoms [19]. These results led to recommendations for including culturally-adapted cognitive behavioral therapy techniques within clinical interventions for chronically-ill Latinos, for example, by addressing cultural factors such as familismo and respeto.

### Study Aims

This study is a randomized controlled trial of a culturally focused psychiatric consultation model for Asian American and Latino American primary care patients with depression (see Figure 1). The *primary aim *of the study is to determine the feasibility, satisfaction and cost associated with implementing a CFP consultation service within a primary care setting at MGH. Additionally, an *exploratory aim *serves to describe (e.g., demographic factors; level of depression; service utilization) the participant patient population at screening, recruitment and enrollment, as well as to determine which, if any, of these variables influence participation in the study (e.g., consent to be contacted).

**Figure 1 F1:**
[figure not shown]
**Clinical Research Intervention Design**.

## Methods/Design

### Overview

This is a randomized controlled trial of the CFP intervention. During the study period, all patients in participating primary care clinics will receive a screening form for symptoms of depression; data on age, gender, race, ethnicity and primary language will be obtained at the time of screening. Asian American and Latino American patients who screen positive for clinical depression will be contacted by study staff and invited to participate in the CFP study. Eligible patients will be randomized either to the intervention arm or usual care based on their primary care provider. Patients in the intervention arm will receive the CFP intervention over two visits and then called at six-months by study staff to administer follow-up questionnaires (described below). Patients in the usual care arm will be called at baseline and at six-month follow-up by study staff to administer questionnaires (described below). To evaluate the cultural components of the study, a number of qualitative interviews will also be conducted with participants in the intervention and usual care arms, and with members of the target population who did not participate in the study. Please see Figure 1 for the study flowchart.

### Description of Intervention

The CFP intervention includes two major components:

1) Patients receiving the intervention will undergo a CFP consultation assessment by a member of a multidisciplinary team of mental health providers (e.g., psychiatrists, psychologists) who are bilingual and/or bicultural, trained in culturally competent techniques, and familiar with the cultures and languages of the clients served. The Engagement Interview Protocol and DSM-IV-TR Cultural Formulation model will be utilized to make a culturally appropriate diagnosis, assess the patient's psychiatric needs in a cultural context, conduct a culturally focused intervention, engage the patient, and make recommendations to the PCP [15,20,21]. The CFP clinician will work collaboratively with the patient's PCP to communicate diagnostic and treatment recommendations after the two-week follow-up visit. Given the critical nature of communicating the CFP findings to the PCP, the CFP clinician will work with the PCP to determine his preferences for communication. Recommendations can be given to the PCP by multiple avenues: by e-mailed letter, and/or by page or phone call as needed. Clinicians will make themselves available to PCPs on an as-needed basis throughout the study period.

2) Patients will receive a culturally appropriate CFP consultation patient toolkit, available in their language of preference (i.e., English, Spanish, Chinese, or Vietnamese), as well as training in using the toolkit materials. The patient toolkit was added to enrich the intervention by providing patients with psychoeducation, handouts on managing depression based on cognitive behavioral therapy techniques, and information on community resources [22]. To help in the management of their depression, patients will be encouraged to complete these materials and bring them to visits with their PCP. In addition, within two weeks of the initial consultation, patients will attend a follow-up visit with the CFP clinician to review and answer their questions about the treatment of their depressive symptoms. The CFP clinician will also review patients' understanding of the toolkit, including their use of the cognitive-behavioral based handouts. To add flexibility in follow-up for patients, these visits can be done in person or over the phone.

### CFP Intervention Training

At the beginning of the study, CFP clinicians attend four hour-long training sessions on the CFP consultation study procedures to ensure that the intervention is applied in a standard fashion. Clinicians will audiotape all CFP sessions, and a weekly group supervision meeting for CFP clinicians will be held to review cases and provide supervision for issues related to clinical diagnosis and intervention. Finally, the CFP consultation service will meet weekly to discuss consultation requests, follow up on the impact of consultations, and to address other logistic issues.

### Inclusion/Exclusion Criteria

Patients will be included based on the following criteria: adults who 1) are 18 years of age or older; 2) are members of either targeted Asian American or Latino American minority groups; 3) screen positive for symptoms of depression; and 4) are able to consent to study participation. Patients will be excluded if they have active unstable, untreated psychiatric illness precluding participation in the study (e.g., actively suicidal or homicidal or actively psychotic). Patients in the intervention arm will be excluded if they have bipolar disorder.

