### Target Health Condition

All patients in the intervention and usual care (control) arms will be screened for clinical depression using the self-rated PHQ-2 at their primary care visit. Both patients and PCPs will be notified of positive screening results for all patients assessed. For the intervention arm, diagnoses of specific depressive disorders (major depressive disorder, dysthymia, depressive disorder NOS, adjustment disorder with depressed mood) will be established during the baseline clinical interview using DSM-IV-TR criteria [21].

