### Analytic Plan

*Description of Measures *(See Table 1):

**Table 1 T1:** Patient measures administered over study period.

PATIENT MEASURES BY TIMEPOINT					
	**Screen**	**Baseline Assessment**	**2 Week Follow-Up^+^**	**6 Month Follow-Up^+^**	**Qualitative Interview^+^**

MINI International Neuropsychiatric Interview (MINI)*		X			

Quick Inventory of Depressive Symptomatology (QIDS-SR)		X		X	

Resource Utilization Questionnaire		X		X	

CFP Consultation, Assessment & Toolkit*		X	X		

Global Assessment of Functioning (GAF)*		X			

Patient Health Questionnaire (PHQ-2)	X				

Patient Satisfaction Questionnaire				X	

Schwartz Outcome Scale (SOS-10)		X	X	X	

Demographic Questionnaire		X			

Qualitative interview					X

*Intervention arm only.

^+ ^Visit may be conducted by phone.

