### Baseline Visit

Both patients in the intervention and usual care arm will give consent to participate in the study at the beginning of the baseline visit. In the intervention arm, assessment measures used at baseline to characterize the intervention patient population will include the Mini International Neuropsychiatric Interview (MINI) [28], Quick Inventory of Depressive Symptomatology-Self Rated Scale (QIDS-SR) (see Appendix 2) [29], Global Assessment of Functioning (GAF) [21], and Schwartz Outcome Scale (SOS-10) [30]. Questionnaires regarding the patients' demographics and utilization of resources will also be assessed. In the usual care arm, for target minorities who screen positive, the assessment measure will include the QIDS-SR and SOS-10.

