### Six-month follow-up

Patients will have the option to complete the visit over the phone or in person. In both the intervention and usual care arms, patients will be given the QIDS-SR self-rated questionnaire and asked a brief "Resource Utilization Questionnaire" with questions regarding use of antidepressant medications, referrals/visits to mental health specialists, or alternative providers both in and out of the MGH system. The electronic medical record will also be reviewed at baseline and at the six-month follow-up for both intervention and usual care arms to obtain depression diagnoses, prescription of antidepressant medications, and referrals/visits to mental health specialists in the system.

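### Bipolar disorder is an exclusion in the intervention arm only, and a diagnostic interview is listed for that arm only, so the between-arm comparisons do not compare like with like

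*Protocol article*

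**What the plan says.** All statements are from the protocol article.

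- **Common exclusion.** Inclusion/Exclusion Criteria first give a rule for everyone: "Patients will be excluded if they have active unstable, untreated psychiatric illness precluding participation in the study".
- **Arm-specific exclusion.** The same section then adds: "Patients in the intervention arm will be excluded if they have bipolar disorder". Nothing equivalent is written for usual care.
- **Allocation.** Overview: "Eligible patients will be randomized either to the intervention arm or usual care based on their primary care provider". Randomization scheme describes matching practices and randomising one of each pair. Under Baseline Visit, consent is taken at the start of that visit, when the arm is already known.
- **Assessment, intervention arm.** Table 1 marks the MINI, the CFP consultation and the GAF as "Intervention arm only". Target Health Condition says "For the intervention arm, diagnoses of specific depressive disorders" will be established at the baseline clinical interview, and describes no such interview for usual care.
- **Assessment, usual care.** Baseline Visit: "In the usual care arm, for target minorities who screen positive, the assessment measure will include the QIDS-SR and SOS-10".
- **Information shared by both arms.** Six-month follow-up: "The electronic medical record will also be reviewed at baseline and at the six-month follow-up for both intervention and usual care arms".
- **Use of the data.** Exploratory analysis compares the arms on QIDS-SR, depression diagnosis and treatment. The cost paragraphs under Qualitative analysis compare them on service use and cost of care.

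**The concern.** Randomisation makes arms comparable only for patients who enter by the same rule. Here a patient with bipolar disorder is ineligible if the provider is in an intervention practice, and eligible if the provider is in a usual-care practice. No chance process balances a filter that depends on arm.

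The planned adjustment does not repair this. Exploratory analysis would add covariates that differ significantly between arms, but the measures listed for usual care do not identify bipolar disorder, so there is nothing to adjust for or restrict on.

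At stake are the exploratory comparisons of symptoms, diagnosis and treatment, and the comparison of utilisation and cost of care. Differences there could partly reflect who was removed from one arm. Diagnosis and treatment rates could shift for this reason even if symptom response were the same in both kinds of patient, because bipolar disorder is not among the depressive disorders listed under Target Health Condition.

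**Working it through.** The plan gives no figure for this exclusion, so there is none to reproduce. The check has two parts.

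**1. Order of events, with the sections side by side**

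| Step | Intervention | Usual care |
|---|---|---|
| Arm set by provider or practice | yes | yes |
| Consent at baseline visit | after arm is set | after arm is set |
| Exclusion for unstable, untreated illness | applies | applies |
| Exclusion for bipolar disorder | applies | not written |
| Diagnostic interview or MINI | listed | not listed |
| Record review at baseline | planned | planned |

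The rows differ at the bipolar exclusion and at the means of detecting it. Overview has eligible patients being randomised, which implies that eligibility is settled before allocation. A criterion that exists only once the arm is known does not fit that order.

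**2. Possible size**

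Inputs from Sample size and power: revised total 120, so 120 / 2 = 60 per arm; planning values 50% and 35%, read here as response proportions, a difference of 15 points.

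Inputs assumed, because the article gives neither:
- f, the share of usual-care patients who would have been excluded in the other arm: 3% to 10%.
- d, response in non-bipolar minus response in bipolar patients: 20 points in either direction.

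Patients without a counterpart among the 60 in usual care: 60 × 0.03 = 1.8 and 60 × 0.10 = 6, so about 2 to 6.

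Suppose there is no true effect and response in non-bipolar patients is r. The intervention arm, with bipolar patients removed, shows r. Usual care shows (1 − f) × r + f × (r − d) = r − f × d. The spurious difference is

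bias = r − (r − f × d) = f × d.

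| f | d = +20 points | d = 0 | d = −20 points |
|---|---|---|---|
| 3% | +0.6 | 0 | −0.6 |
| 10% | +2.0 | 0 | −2.0 |

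A positive sign favours the intervention.

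A wider set of assumptions, with r = 35%:
- f = 5%, bipolar response 30%: usual care 0.95 × 35 + 0.05 × 30 = 34.75%, bias 0.25 points.
- f = 20%, bipolar response 10%: usual care 0.80 × 35 + 0.20 × 10 = 30.0%, bias 5.0 points, and 60 × 0.20 = 12 patients without a counterpart.

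Against the 15-point planning difference these are 0.25 / 15 = 2% and 5.0 / 15 = 33%.

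For scale, the standard error of the difference at 60 per arm, before clustering, is √[(0.50 × 0.50 + 0.35 × 0.65) / 60] = √(0.4775 / 60) = 0.089, or 8.9 points. A bias of 0.6 to 2 points is 0.6 / 8.9 = 7% to 2 / 8.9 = 22% of that.

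No figure can be given for cost, because the article describes neither costs nor service use in bipolar patients.

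**The case against.** The strongest case against is about importance. The primary aim is feasibility, satisfaction and cost. Feasibility, satisfaction with the service and the cost of running it do not depend on balance between arms. The outcome comparisons are labelled exploratory, the service-use comparison is called preliminary, and the reduced sample is justified as informing later designs. Under the narrower assumptions the bias is well below one standard error. All of this stands and lowers the severity. It does not remove the defect: a small sample makes an estimate imprecise, whereas this makes the comparison unequal by construction, and the between-arm cost of care does touch the primary aim.

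A second objection is practical. Recruitment had begun, so new wording cannot recover patients already excluded. Recorded diagnoses may also be incomplete in a population that the Background describes as prone to misdiagnosis. Both points stand and are reflected in the fix.

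Some stronger readings are tempting but not supported:

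- **That bipolar patients do worse, so the bias favours the intervention, or that they use more services, so cost is biased more.** The article says nothing on their prognosis or service use.
- **That the MINI is the tool that applies the exclusion.** This is a fair inference, but Baseline Visit says only that the baseline measures characterise the intervention population. Neither tool nor timing of the exclusion is stated.
- **That suicidality and psychosis are also checked by a clinician in one arm only.** Those exclusions are written for all patients, and the article does not say who checks them.
- **That an intention-to-treat set is broken.** The article defines no such set, and analysis sets are commonly left to an analysis plan, which is not at hand.

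**Conclusion.** The point holds in this form: the bipolar exclusion is written for one arm, the only diagnostic interview is listed for that arm, and the arm is fixed before consent and baseline. Followed as written, the plan gives arms with different eligibility and then compares them.

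The direction is unknown. Under the assumptions of 3-10% affected and a 20-point response difference either way, the bias is 0.6 to 2 points; the wider set reaches 5 points; equal response gives zero for symptom response. These sizes rest wholly on assumed prevalence and prognosis. The loss of comparability does not.

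Severity is moderate. The effect falls on the exploratory outcome comparisons and the preliminary between-arm comparison of utilisation and cost.

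**What to change.** 1. Reconcile Overview, Inclusion/Exclusion Criteria, Randomization scheme and Table 1 so that one eligibility rule, applied from one information source, holds in both arms. The baseline record review is already planned for both and could serve. The diagnosis should be taken as recorded before the baseline visit, so that the consultation cannot feed the record in one arm.
2. Keep patients identified as bipolar only at the intervention-arm interview in six-month follow-up and analyse them as allocated, whatever clinical rule governs delivery of the consultation.
3. Report their number, with a sensitivity analysis without them. That analysis again removes patients from one arm only, so it should not replace the main one.
4. Where patients have already been excluded, report how many, and describe the between-arm comparisons as subject to differential exclusion.

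The cost is a wording amendment, one added field in the record review and continued follow-up of a few patients. The downsides are that some patients who may not receive the full intervention count in its arm, and that recorded diagnoses may be incomplete. The second step protects the comparison even where the record misses a diagnosis.
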